### Statistical analyses

Baseline characteristics and analytical data will be summarised using descriptive statistics inclusive of mean, median, range, SD and absolute as well as relative frequencies depending on the nature of data. A logistic regression model will be used to identify characteristics of TB among ICs, households and HHCs that are predictive of incident TB. From the study database, we will simulate algorithms of different tests to obtain the testing combination with the best accuracy. We will couple tests with a mathematical model that quantifies the risk of infection and/or disease to enhance predictive performance. The reporting of the development of the prediction model will follow the Transparent Reporting of a multivariable prediction model for Individual Prognosis Or Diagnosis Initiative.^38^

The validation of novel diagnostic tests for detecting TB will be analysed as a 1:4 matched nested case–control study with HHCs diagnosed with TB at baseline and during follow-up serving as cases, and HHCs who do not develop TB during follow-up as controls; controls will be matched for site, age, sex, HIV status and other risk factors for developing TB. Sensitivity and specificity of novel tests will be determined using pre-existing positive/negative cut-offs where these exist^39^; and receiver operating curves (ROC) constructed with area under the ROC curve calculated. For tests aiming to identify individuals at high risk of TB in the future, only HHCs who are diagnosed with TB during follow-up will serve as cases (ie, those diagnosed with TB at baseline will be excluded). Stored samples from all timepoints will be retrieved and diagnostic accuracy (ie, sensitivity and specificity) of the novel test determined at different timepoints before TB diagnosis. The decision of assigning the ‘active TB’ endpoints to participants will be blinded from the new test results to avoid inclusion bias.

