**Methods and analysis:**

A total of 2100 HHCs (aged ≥10 years) of adults with microbiologically-confirmed pulmonary TB will be recruited and followed up at 6-month intervals for 18–24 months. At each time point, a WHO symptom screen and digital chest radiograph (dCXR) will be performed, and blood and urine samples will be collected. Individuals screening positive (WHO symptom screen or dCXR) will be requested to provide sputum for Xpert MTB/Rif Ultra. At baseline, HHCs will also be screened for HIV, diabetes (HbA1c), chronic lung disease (spirometry), hypertension and anaemia. Study outcomes will be coprevalent TB (diagnosed at enrolment), incident TB (diagnosed during follow-up) or no TB at completion of follow-up. Novel diagnostics will be validated using fresh and biobanked samples with a nested case–control design. Cases are defined as HHCs diagnosed with TB (for early diagnosis) or with incident TB (for prediction of progression) and will be matched by age, sex and country to HHCs who remain healthy (controls). Statistical analyses will include assessment of diagnostic accuracy by constructing receiver operating curves and calculation of sensitivity and specificity.

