## Methods and analyses

### Study objectives

ERASE-TB’s primary objectives are (1) to determine the sensitivity and specificity of novel diagnostics to detect TB, in particular, asymptomatic or minimally symptomatic TB, (2) to evaluate novel diagnostics for detection of likely TB progression and (3) to enhance the performance of novel diagnostics by simulating testing algorithms coupled with individual risk estimates from a mathematical model. The secondary objectives are (1) to determine the TB prevalence among household contacts (HHCs) of infectious TB index cases (ICs) at baseline and during 18–24 months follow-up, (2) to establish a biorepository of cryopreserved specimens from HHCs for future development and validation of diagnostic tests and (3) to assess the association of selected chronic disease conditions and TB among HHCs.

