#### Household contacts

Informed consent is obtained from all eligible adult HHCs. For HHC <18 years of age, the guardian is asked to provide informed consent, with assent also sought from children dependent on local guidance. At baseline, a questionnaire is administered collecting information on socioeconomic and demographic characteristics, previous medical history of TB, HIV and other diseases, exposure risk factors, smoking and alcohol history. The physical examination includes height, weight, mid-upper arm circumference and blood pressure measurement. In addition, all HHCs are offered free HIV testing according to the National Guidelines. All people with confirmed HIV infection will have CD4 counts performed and be referred for TB preventive therapy. Those not yet on antiretroviral therapy (ART) and those who interrupted ART are referred for ART at local services.

Point of care HbA1c (A1cCare, SD Biosensor, Gyeonggi-do, Republic of Korea) and haemoglobin (Hemocue 301+, Hemocue, Angelholm, Sweden) tests and spirometry (including prebronchodilation and postbronchodilation with inhaled salbutamol) are performed at baseline or the 6-month visit. HHCs who did not take up HIV testing or other screening at baseline are offered these tests at each study visit. Any HHCs with test results requiring treatment or further investigations are referred for respective services.

HHCs are screened for TB using the WHO symptom screening questionnaire and a dCXR, reviewed by a clinical officer. dCXRs are not performed in pregnant HHCs. HHCs with a positive WHO symptom screening and/or abnormal dCXR are asked to provide sputum samples for TB investigations, that is, for GeneXpert and mycobacterial culture. Those with negative symptom screen and normal dCXR are asked to provide a spontaneous sputum sample for storage (with sputum induction performed if required).

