At baseline, urine, serum, plasma, whole blood (native, and with RNA preservation in PAXgene tubes (BD Biosciences, New Jersey)) are stored. A finger-prick sample is taken and investigated using the Xpert TB Host Response RUO Prototype cartridge (Cepheid, Sunnyvale, California). T-cell Activation Marker Tuberculosis (TAM-TB) assay and Interferon Gamma Release Assay (IGRA; STANDARDTM F TB-Feron FIA (IFN-gamma; SD Biosensor, Republic of Korea) are performed on fresh venous blood. In Tanzania and Mozambique, storage of peripheral blood mononuclear cells for later characterisation of the TB-specific immune response is also performed.

Procedures for follow-up and unwell visits are similar to those at baseline. Measurement of HIV status, haemoglobin (HB), HbA1c, spirometry, CD4 count and IGRA testing are not performed at follow-up visits, unless not done previously. At the last scheduled visit, all HHCs not known to have HIV are reoffered HIV testing and a spontaneous or induced sputum sample is stored for all participants.

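### For same-visit detection of current TB, the study database will show near-100% sensitivity for symptom/dCXR entry and almost no added yield for a blood or urine test, whatever the truth

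*Protocol article*

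**What the plan says.** Primary objective 3 (Study objectives) is "to enhance the performance of novel diagnostics by simulating testing algorithms coupled with individual risk estimates from a mathematical model". The Statistical analyses section gives the method: "From the study database, we will simulate algorithms of different tests", the aim being to find the most accurate combination. The only TB outcome the article describes is the study endpoint: coprevalent TB, incident TB, or no TB.

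How a contact comes to be tested for that endpoint is stated in three places:

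- Abstract, Methods and analysis: "Individuals screening positive (WHO symptom screen or dCXR) will be requested to provide sputum for Xpert MTB/Rif Ultra".
- Household contacts: "HHCs with a positive WHO symptom screening and/or abnormal dCXR are asked to provide sputum samples for TB investigations". The section on contacts who screen positive repeats this.
- Study design: unwell visits follow from the participant feeling unwell or from an abnormal finding, with dCXR as the example.

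For everyone else, the Household contacts section says: "Those with negative symptom screen and normal dCXR are asked to provide a spontaneous sputum sample for storage". At the last scheduled visit, "a spontaneous or induced sputum sample is stored for all participants". The article does not say that this stored sputum is tested to define the endpoint.

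Assignment of the TB endpoint "will be blinded from the new test results to avoid inclusion bias" (Statistical analyses). Controls are contacts with no TB diagnosis during follow-up. The Novel test candidates section lists computer-read dCXR and Xpert Ultra alongside the urine, T-cell, transcriptomic and protein tests.

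**The concern.** This is partial verification: the reference standard is applied only to people already flagged by one of the tests being compared. A contact whose TB is missed by both symptoms and dCXR is recorded as free of TB at that visit. Blinding of the endpoint is sound protection against incorporation bias, but it also means that a positive blood or urine test does not lead to verification.

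When algorithms are ranked on this database for detection of current TB, the screen's sensitivity is set by design and not measured. A test whose value lies in finding TB that the screen misses cannot show that value at the same visit. Objective 1 puts particular weight on asymptomatic and minimally symptomatic TB, so a ranking that favours the existing entry step regardless of the facts could mislead on a central question.

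**Working it through.** **1. The plan's own figures.** From Sample size: 2100 contacts, 64 TB cases (3%), of which 49 incident and 15 coprevalent, and 196 controls for the 49. Check: 0.03 × 2100 = 63 against 64 stated (64/2100 = 3.05%); 49 + 15 = 64; 4 × 49 = 196. Exact (Clopper–Pearson) 95% intervals: 36/49 gives 58.9–85.0%, 40/49 gives 68.0–91.2%, 180/196 gives 87.1–95.3%, 184/196 gives 89.6–96.8%. All match the stated intervals after rounding. They concern tests for incipient infection. The article gives no figure for the accuracy of an algorithm or of the symptom/dCXR screen.

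**2. The paired table at the diagnosing visit.** Classify people with TB as *a* (screen positive, novel test positive), *b* (screen positive, novel negative), *c* (screen negative, novel positive) and *d* (both negative). Because sputum is examined only after a positive screen, *c* and *d* are essentially empty in the database. So:

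- apparent sensitivity of the screen = (a + b)/(a + b) = 100%, i.e. 15/15 coprevalent cases and up to 64/64 at the diagnosing visit;
- apparent sensitivity of the novel test = a/(a + b), which can tie with the screen at best;
- apparent sensitivity of screen or novel test = 100%, so the apparent gain is 0.

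None of this depends on the true accuracy of either test.

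**3. What is hidden.** Let *s* be the true sensitivity of the screen. This is an assumption; the documents do not give it. Missed per 15 found = 15(1 − s)/s. The true gain from adding a novel test is (1 − s) × r, where *r* is its sensitivity among screen-negative TB, so it lies between 0 and 1 − s.

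| Assumed s | Missed at baseline per 15 found | Largest possible true gain | Apparent gain |
|---|---|---|---|
| 70% | 6.4 | 30 points | 0 |
| 80% | 3.7 | 20 points | 0 |
| 90% | 1.7 | 10 points | 0 |

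Over a wider range, s = 60% gives 10.0 missed and s = 95% gives 0.8. If a novel test's true sensitivity exceeds *s*, its sensitivity ranking against the screen is reversed, or at best tied, in the database.

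**4. Effect on specificity.** With 10% loss to follow-up, contacts without a TB diagnosis number about 2100 × 0.9 − 64 = 1826. If none of the baseline misses ever surfaced, they would make up 1.7/1826 = 0.09% to 6.4/1826 = 0.35% of that group. Among 4 × 64 = 256 controls for the detection analysis, sampled without regard to matching, that is 256 × 1.7/1826 = 0.2 to 256 × 6.4/1826 = 0.9 people. A correct positive in them counts as a false positive, but the effect of baseline misses is small. The distortion is mainly in sensitivity.

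**5. What escapes the problem.** For the 49 incident cases, stored samples from earlier visits are tested. At the pre-diagnosis sensitivities quoted in Novel test candidates for transcriptomic signatures (25% to 48%), 49 × 0.25 = 12 to 49 × 0.48 = 24 cases would be positive at an earlier visit and credited as lead time.

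**The case against.** The strongest reply is that the article never says algorithms will be compared with symptom/dCXR entry. It names no reference standard for the simulation, and it ties objective 3 to a risk model meant to improve prediction. An article may leave such detail to the full protocol or analysis plan. Other points support this:

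- Contacts are rescreened every six months for 18–24 months (four or five scheduled screens), so TB missed once may surface later as incident TB, where earlier positive tests are credited.
- dCXR is done whatever the symptoms (except in pregnancy), so symptom-free TB visible on dCXR does enter the endpoint.
- The telephone visit after the last scheduled visit (Figure 3, note B) may record TB diagnosed elsewhere.
- The stored sputum could still be tested.
- Best accuracy includes specificity, so a novel test can win there or on sputum tests saved.

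Most of this stands, and it confines the point to same-visit detection. It does not remove it. Computer-read dCXR and Ultra are themselves candidate tests, so parts of the screening pathway are inside the set of combinations. Scoring on the study endpoint is an inference, but no other TB outcome is described. Rescreening gives lead time, not the yield missed at a given visit. An analysis plan cannot recover verification that was not done; it can only add verification or narrow the claim.

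**Conclusion.** The point holds for same-visit detection of current TB: strictly for the 15 expected coprevalent cases (23% of 64), and for the diagnosing visit of the incident cases. There, the sensitivity of symptom/dCXR entry is close to 100% by design, and the added yield of a blood or urine test among screen-negative contacts is about 0 whatever its true value. Under an assumed true screen sensitivity of 70–90%, about 2–6 baseline cases go unseen per 15 found. The direction does not depend on that assumption; the size does.

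A reader might infer more, and the documents do not support it:

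- That no algorithm entered by a novel test can show any benefit under objective 3. Prediction, lead time, specificity and sputum tests saved all remain open.
- That the screen's sensitivity is exactly 100%. TB diagnosed elsewhere may be captured by telephone, although the article does not say whether it counts as an endpoint.
- That the loss should be computed on all 64 cases: 64(1 − s)/s, or 7 to 27 missed, most of them then scored as false positives. This treats every miss as permanent, although 49 of the 64 are incident cases with earlier samples. Applying the 82% sensitivity to those misses would also borrow a figure that Sample size gives for incipient infection.

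**What to change.** In Statistical analyses, for current TB:

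1. Compare algorithms only as a second (triage) step within contacts positive on symptom screen or dCXR. Report sensitivity relative to the TB cases found and the number of sputum tests saved.
2. State that two quantities cannot be estimated from the database: the sensitivity of the symptom/dCXR step, including computer-read dCXR, and the added yield of algorithms entered by a novel test.
3. Keep prediction of incident TB and lead time from earlier stored samples as separate analyses.

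This costs one paragraph and a narrower claim, with no new data, and is enough to prevent the wrong conclusion.

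Optional, at extra laboratory cost: test stored sputum from a sample of screen-negative contacts, drawn by real-time test result (positives, plus a random sample of negatives), and weight each result by the inverse of its sampling fraction. This would let the added yield be estimated, with precision limited by the few cases expected.

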### Sample size

An estimated 800 to 900 TB-confirmed ICs are required for the subsequent enrolment of an anticipated 2100 HHCs, that is, 700 HHCs per country. Loss to follow-up of HHCs is estimated to be 10%. A total of 64 HHCs (3%) are estimated to be diagnosed with TB during the study period, based on previous active case finding studies among HHCs.^16^ Validation for subclinical and early TB will include incident (n=49) and coprevalent TB cases (n=15). Validation for detection of incipient *Mtb* infection will include samples of participants with incident TB (n=49) matched 1:4 to samples of participants without TB (n=196). For tests diagnosing incipient *Mtb* infection sensitivities of 73% and 82% would be detected with a precision of 59%–85% and 68%–91%, respectively. For specificities of 92% and 94%, the CIs would be 87% to 95% and 90% to 97%.

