### Novel test candidates

A range of novel test candidates targeted at pathogen detection or identification of host responses to *Mtb* are being applied, either in real-time (for all participants) or retrospectively (in a case–control design). While a number of novel test candidates have been prespecified, the ERASE-TB biobanking processes allow for addition of further candidate tests to be evaluated on stored samples as they become available.

DCXRs offer good sensitivity for diagnosis of pulmonary TB. However, high interinvestigator and intrainvestigator variability, and lack of trained interpreters presents a barrier to implementation in many high-TB burden settings. Computer-aided interpretation systems, such as CAD4TB (Delft Imaging, Hertogenbosch, Netherlands) and qXR (Qure.ai, India), may increase image-reading capacity, with good performance, and serve, therefore, as a systematic screening tool to identify individuals in need of confirmatory TB tests.^17 18^

Xpert MTB/RIF Ultra is a nucleic acid amplification test for *Mtb* with a lower limit of detection compared with the previous Xpert MTB/RIF generation, and, therefore, conferring higher sensitivity in paucibacillary specimens. This, however, comes at the expense of specificity, particularly in high TB incidence settings, resulting in ‘false positives’.^19^ WHO guidelines recommend Xpert MTB/RIF Ultra for TB diagnosis among adults and children acknowledging that further evaluation, particularly of the role of Xpert MTB/RIF Ultra for TB screening, is needed.^20 21^

FLOW-TB is an advanced ELISA for the detection of *Mtb* lipoarabinomannan (a mycobacterial cell wall component) in urinary specimens with results available within 65 min.^22^

The TAM-TB detects Mtb-specific CD4 T-cells through in vitro antigen stimulation with *Mtb*-derived peptides, that is, from ESAT-6 to CFP-10, followed by flow cytometry. TAM-TB discriminated latent *Mtb* infection from TB in freshly collected blood with 83% sensitivity and 96%–98% specificity in previous studies. Furthermore, TAM-TB may detect early TB disease progression up to 9 months prior to the identification of *Mtb* in sputum.^23–25^

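### Novel tests run in real time on all contacts are assigned to a 1:4 matched nested case–control validation, which makes their specificity intervals roughly two to three times wider than the full cohort would give

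*Protocol article*

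**What the plan says.** Three places in the protocol article bear on how a novel test is evaluated.

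- Statistical analyses: "The validation of novel diagnostic tests for detecting TB will be analysed as a 1:4 matched nested case–control study". Controls are to be matched on site, age, sex, HIV status and further TB risk factors. No exception is made for tests that every participant receives.
- Abstract, Methods and analysis: "Novel diagnostics will be validated using fresh and biobanked samples with a nested case–control design". Fresh-sample tests are therefore expressly included.
- Novel test candidates: the candidates "are being applied, either in real-time (for all participants) or retrospectively (in a case–control design"). Some tests are thus run on the whole cohort.

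The Household contacts section shows which tests these are. At baseline a finger-prick sample goes to the Xpert TB Host Response cartridge, and TAM-TB is done on fresh venous blood. Novel test candidates confirms that the cartridge is to be evaluated on freshly collected specimens.

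The Sample size section gives specificity precision only for the matched progression analysis, in which incident cases are "matched 1:4 to samples of participants without TB (n=196"). For TB detection it says "Validation for subclinical and early TB will include incident (n=49) and coprevalent TB cases (n=15") but gives no control number. No section describes a full-cohort specificity estimate for a single test.

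**The concern.** Nested case–control sampling is efficient when each assay costs money or uses up stored material. That reason disappears for a test already performed on every contact, because the results on TB-free contacts exist whether or not they are analysed.

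Specificity is half of the first primary objective. The protocol expects about 3% of contacts to be diagnosed with TB, so false positives will outnumber true positives for any test with specificity in the low nineties, and small changes in specificity matter. Two things are lost if the text is followed as written:

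- **Precision.** The interval rests on a few hundred controls when about 1,800 to 2,000 TB-free contacts are available.
- **Target population.** Crude specificity among controls selected to resemble cases need not equal specificity among all contacts, and predictive values cannot be read directly from a 1:4 sample.

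**Working it through.** **Inputs (Sample size section).** "enrolment of an anticipated 2100 HHCs, that is, 700 HHCs per country"; "A total of 64 HHCs (3%) are estimated to be diagnosed with TB during the study period"; loss to follow-up 10%; 49 incident and 15 coprevalent cases; 196 controls for progression; 800 to 900 index cases. The confidence level is not stated; 95% two-sided is assumed.

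**Step 1: reproduce the plan's figures.** Exact (Clopper–Pearson) intervals with counts rounded to whole numbers:

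- specificity 92%: 180/196 gives 87.1–95.3% (stated 87–95%)
- specificity 94%: 184/196 gives 89.6–96.8% (stated 90–97%)
- sensitivity 73%: 36/49 gives 58.9–85.1% (stated 59–85%)
- sensitivity 82%: 40/49 gives 68.0–91.2% (stated 68–91%)

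All four agree to the nearest percent, so the same method is used below.

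**Step 2: TB-free contacts available.** Without loss: 2100 − 64 = 2036. After 10% loss: 0.9 × 2100 − 64 = 1826.

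**Step 3: controls used.** Progression: 49 × 4 = 196, as stated. Detection: (49 + 15) × 4 = 256, derived because the protocol does not give it.

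**Step 4: share of TB-free contacts left out.**

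- Detection: 1 − 256/1826 = 86.0%; 1 − 256/2036 = 87.4%
- Progression: 1 − 196/1826 = 89.3%; 1 − 196/2036 = 90.4%

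**Step 5: exact 95% interval at specificity 92%.**

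| Analysis | TB-free contacts | Interval | Width (points) |
|---|---|---|---|
| Progression, 1:4 | 196 | 87.1–95.3% | 8.2 |
| Detection, 1:4 | 256 | 88.2–95.2% | 7.0 |
| Full cohort after 10% loss | 1826 | 90.7–93.2% | 2.55 |
| Full cohort, no loss | 2036 | 90.7–93.1% | 2.4 |

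Width ratios are 2.7 to 2.9 for detection and 3.2 to 3.4 for progression. At specificity 94% they are almost the same (2.75 to 2.9 and 3.2 to 3.4).

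**Step 6: allow for household clustering.** Mean household size m = 2100/850 = 2.47, taking the midpoint of 800 to 900 index cases. Design effect = 1 + (m − 1) × ICC, which is 1.07 at ICC 0.05 and 1.44 at ICC 0.3 (both ICCs assumed). Charging this to the full cohort only, the width ratio is approximately √(N / (design effect × n)):

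- smallest: √(1826 / (1.44 × 256)) = 2.2
- largest: √(2036 / (1.07 × 196)) = 3.1

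At ICC 0.3 the full-cohort interval is about 3 points wide (2.55 × √1.44 = 3.1).

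**Step 7: what the width means in use.** False positives per 1,000 TB-free contacts are 1,000 × (1 − specificity). The 256-control interval spans 48 to 118; the full-cohort interval after loss spans about 68 to 93.

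**The case against.** The strongest reply is that nothing in the article forbids a full-cohort analysis. Novel test candidates already links the case–control design to retrospective testing, and the Statistical analyses paragraph goes on to describe retrieving stored samples. An article condenses, and an analysis plan not shown here may separate the two kinds of test. This has some force: the text may misdescribe the intention. It does not remove the point. Novel test candidates says how tests are applied, whereas the Abstract and Statistical analyses say how they are validated, and the Abstract names fresh samples. If a full-cohort analysis is intended, those two sentences are wrong and need the same correction.

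A reader might infer more than the documents support:

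- *That the remaining results are discarded.* They are not. The algorithm simulation draws on the study database and is not confined to the matched subset. Only the single-test specificity estimate is affected.
- *That every fresh or imaging test is affected.* IGRA is performed but is not described among the novel candidates. Computer-aided radiograph reading is not said to be run in real time on everyone, and pregnant contacts have no radiograph.
- *That 90% and a factor above three apply throughout.* Those figures belong to the 196-control progression analysis. The detection analysis that the Statistical analyses sentence describes gives 86–87% and 2.7 to 2.9.
- *That the matched design is invalid.* It is valid, and sensible for stored samples. Predictive values could also be recovered by weighting if the control-sampling probabilities are kept.

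It is also fair to say that the small number of cases is the tighter limit. With 49 incident cases the sensitivity intervals stay at 59–85% and 68–91% whichever controls are used, and the article acknowledges that limitation.

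**Conclusion.** The point holds for tests performed in real time on all participants, clearly the Xpert TB Host Response cartridge and TAM-TB. Followed as written, the protocol would give them a specificity interval 2.7 to 3.4 times wider than the cohort allows, or roughly 2.2 to 3.1 times with clustering, in a population matched to cases. This is an avoidable loss of efficiency and representativeness, not a bias in sensitivity or an error in the stated intervals.

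The size rests on four assumptions: one valid result per contact, so missing or invalid tests would shrink the gain; 256 detection controls, inferred from the 1:4 ratio; intraclass correlations that are not in the documents; and roughly equal household sizes. None of these reverses the direction.

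**What to change.** Reconcile the Abstract, Novel test candidates and Statistical analyses by splitting the validation according to how a test is run:

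- For tests performed in real time on all participants, estimate sensitivity, specificity, AUC, PPV and NPV in the full cohort, with confidence intervals that allow for household clustering. Name the tests in this group.
- For assays run retrospectively on stored samples, keep the 1:4 matched nested case–control analysis.
- In Sample size, add the expected full-cohort specificity precision (about 2.5 points wide at 92%, about 3 with clustering at ICC 0.3) and state the number of controls for the TB-detection analysis.

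The cost is a change of wording and a little extra analysis. No additional samples, tests or participants are needed.
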